## Abstract

**Introduction::**

Prediabetes is a high-risk stage of transition to type 2 diabetes mellitus. Previous studies suggest that acupuncture has potential to prevent prediabetes’ conversion to type 2 diabetes mellitus, which lack of high-quality evidence. Zuo's acupuncture, a kind of acupuncture technique, is formed through long-term and repeated clinical practice by professor [name] who integrates the internal meaning of Dong extra acupoints and Taoist medicine principle according to the theories of traditional Chinese medicine. It is used clinically to increase the regression toward normo-glycemi on prediabetes. The objective of this trial is to clarify the clinical effectiveness and safety of Zuo acupuncture for prediabetes.

**Methods and analysis::**

This study is a prospective randomized controlled trial in which 60 patients with prediabetes will be randomly allocated in a 1:1 ratio into either an acupuncture treatment group or a control group. Prediabetes patients in the control group will receive prediabetes health education for lifestyle interventions, whereas patients in the acupuncture group will receive lifestyle interventions plus Zuo Daliji and Yueku stitch treatment. Twenty-four treatment sessions will be performed over 3 months. The primary outcome is conversion rate from prediabetes to normal blood glucose. Secondary outcomes include fasting plasma glucose, 2-hour plasma glucose, glycosylated hemoglobin and blood lipid concentration.

**Ethics and dissemination::**

This study was approved by the Ethics Committee of Guangdong Provincial Hospital of Chinese Medicine (permission number: YF2020-107-01) and the protocol conforms to the principles of the Declaration of Helsinki. Data collection will be completed by June 2022. Publications will be ready for submission in July 2022.

## Introduction

1

Prediabetes, also known as impaired glucose regulation, is an intermediate metabolic state between normo-glycemia and diabetes, including 2 states of impaired fasting blood glucose and impaired glucose tolerance (IGT), or both.^[1]^ According to a report released by the International Diabetes Federation in 2017, the total number of adults (aged 20–79) diagnosed with type 2 diabetes mellitus (T2DM) is 425 million, accounting for 8.3% of the total population.^[2]^ In addition to overt diabetes, there are 352.1 million people with prediabetes worldwide, which are expected to increase to 531.6 million by 2045.^[3]^ In 2013, the standardized prevalence of diagnosed and undiagnosed diabetes among Chinese adults was 10.9%, while the prevalence of prediabetes was 35.7%.^[4]^ The American Diabetes Association expert panel thought that up to 70% of prediabetic patients will eventually develop diabetes.^[5]^ Relevant data point out that prediabetes is associated with an increased risk of composite cardiovascular events, coronary heart disease, stroke, and all cause mortality.^[6]^ Therefore, controlling the progression of prediabetes which is a reversible condition into diabetes has become a significant public health issue.

Appropriate interventions in the prediabetes stage can prevent and delay the prediabetes’ conversion to T2DM. For prediabetic individuals, lifestyle modification is the cornerstone of diabetes prevention.^[5]^ Measures taken including changes in healthy diet, moderate exercise, regular rest schedule, and relaxed mood. The “Global Diabetes Report”^[7]^ published by the World Health Organization in 2016 pointed out that diet and physical activity interventions are more effective than drugs in preventing diabetes. The earlier the prediabetes get active intervention, the lower the risk of diabetes. Therefore, searching for effective therapies for prediabetes is in demand. However, there are some deficiencies in changing lifestyles, such as insufficient self-discipline, individual differences, limited environmental conditions, and long maintenance time.

As one of the main nondrug therapies, acupuncture has the potential to treat diabetes and prediabetes. Studies have shown that acupoint catgut embedding therapy can improve the conversion rate of prediabetes to normal glucose tolerance, reduce the incidence of diabetes, and have a lasting effect.^[8]^ Although there are few research reports on the treatment of prediabetes with simple acupuncture, there are still many studies on acupuncture to control blood glucose. A pilot randomized placebo-controlled trial have shown that 30 minutes of needling at CV-12 might be useful in reducing blood glucose level in patients with T2DM.^[9]^ A systematic review and meta-analysis of acupuncture for T2DM suggests that acupuncture is beneficial to improving blood glucose control, lipid control and blood pressure control, and weight loss, compared with sham acupuncture or no acupuncture control group.^[10]^

[name] comprehended the principles of Dong extra acupoints, combined with Taoism, and established a simple and delicate acupuncture system based on traditional acupuncture. Zuo acupuncture has the advantages of less acupuncture points, simple operation, and no need for acupuncture sensation, which may reduce patients’ pain and fear. Zuo acupuncture has achieved good effect in regulating blood glucose and treating diabetic complications by controlling blood glucose. Zuo Daliji and Yueku stitch are a type of Zuo acupuncture. In a randomized controlled trial, Zhu Jingzhi was given hypoglycemic drugs and methylcobalamin and prostaglandin E1 in the control group (n = 30), and the treatment group (n = 30) combined with Daliji stitch and microcollaterals thorning blood therapy on the basis of oral drugs. The results show that the Daliji stitch combined with micro-collateral puncture can significantly relieve and improve the clinical symptoms of patients with diabetic peripheral neuropathy.^[11]^ Li Yang divided 60 patients with prediabetes into a control group (n = 30) and an acupuncture group (n = 30). The control group was given relevant education to improve lifestyle. The acupuncture group was treated with Zuo Liji stitch based on lifestyle intervention. The result shows that acupuncture Liji stitch can more effectively reverse the prediabetes to normal blood glucose.^[12]^ On the basis of point selection of LiJi stitch, Zusanli (ST36), dacha and Taichong (LR3) are added, which is Zuo Da Li Ji and Yue Ku stitch. This treatment is effective in controlling blood glucose and help restore normal blood glucose levels in patients with prediabetes. However, the exclusive effectiveness of Zuo Daliji and Yueku stitch in individuals with prediabetes is not well documented. The objective of this trial is to clarify the clinical effectiveness and safety of Zuo Daliji and Yueku stitch for prediabetes.

## Methods and analysis

2

### Study design

2.1

This study is a prospective randomized controlled trial. It is planned to be conducted from January 1, 2021 to June 1, 2022 in the Traditional Chinese Medicine Hospital of Guangdong Province of China. Prediabetic patients who entered the trial will be randomly assigned to a control group and a treatment group, with 30 cases in each group. Participants in the control group will receive prediabetes health education for lifestyle interventions, whereas patients in the acupuncture group will receive lifestlye interventions plus Zuo Daliji and Yueku stitch treatment. Figure 1 demonstrates the flow of subjects through the trial.

**Figure 1 F1:**
[figure not shown]
Route diagram of study design.

This study protocol conforms to the standard protocol items: recommendations for interventional trials guidelines. Before randomization, all eligible participants will be asked to sign an informed consent.

### Sample size

2.2

The sample size calculation is based on the 2017 randomized controlled trial report of Ning et al^[8]^ who used acupoint catgut embedding to treat prediabetic patients. In this study, the reversal rate of impaired glucose regulation to Normal Glucose Tolerance is estimated as the outcome. We assume that after 3 months of treatment, the reversal rate of the treatment group is 57% and the reversal rate of the control group is 20%. The test levels (α = 0.05 and β = 0.2) are set. The PASS 2008 software (Beijing HuanZhongRuiChi Technology Co., Ltd.) calculates that the sample size of each group is 25, and 50 in the 2 groups. Assuming 15% drop out, a total of 60 participants will be needed to achieve statistical significance, so each group is required to have 30 participants.

### Participants

2.3

We will publicize online and post posters to let the public know the details of the research after obtaining ethical approval. Interested patients can contact our research center for more information before participating in the study. Only after the laboratory test meets the selection criteria can they participate. Patients and the public will not be involved with the design, or conduct, or reporting, or dissemination plans of the research.

### Inclusion criteria

2.4

Participants meeting the following inclusion criteria will be included:

(1)Meet the diagnostic criteria of prediabetes:Participants meet one or both of the following criteria can be diagnosed. (According to the WHO criteria for a diagnosis of prediabetes in 1999^[13]^ which is cited by the Guidelines for the prevention and treatment of type 2 diabetes in China [2017 edition]^[10]^):**Impaired Fasting Glucose**: 6.1 mmol/L ≤ fasting plasma glucose (FPG) < 7.0 mmol/L, and 2-hour plasma glucose (2-hPG) after a 75 g oral glucose tolerance test (OGTT) <7.80mmol/L.**IGT**: FPG < 7.0 mmol/L, and 7.8 mmol/L ≤ 2-hPG (OGTT) < 11.1 mmol/L(2)Aged 18 to 65 years (either sex)(3)Voluntary participation and informed consent signed

### Exclusion criteria

2.5

To reduce the distracting factors of research, participants with any of the following exclusion criteria will be excluded:

(1)Patients who have been taking hypoglycemic drugs and lipid-lowering drugs in the past 3 months(2)Patients who have received acupuncture treatment in the past 1 month(3)Patients who have severe fear of acupuncture and refuse acupuncture treatment(4)Patients with severe cardiovascular and cerebrovascular diseases, liver and kidney dysfunction, blood system diseases or other serious life-threatening diseases, mental illnesses(5)Pregnant or lactating women(6)Body mass index ≥ 28 kg/m^2^

### Randomization procedure and concealment of allocation

2.6

Clinicians will recruit volunteers who meet the research criteria. Patients entering the trial will be randomly assigned to a treatment group or a control group. Randomization will be programmed with SAS 9.2 in the clinical Research and data Center of Guangzhou University of Chinese Medicine. A computer-generated block assigned participants to a treatment or control group on a 1:1 scale. A staff member, independent of this study, will complete the random assignment. The random list will be kept strictly confidential until the study began.

### Intervention

2.7

A total of 60 patients with prediabetes will be recruited. The patients will be randomly assigned to 2 different groups: the treatment group and the control group. Participants in the control group will receive prediabetes health education for lifestyle interventions for 12 weeks, whereas participants in the acupuncture group will receive lifestyle interventions plus Zuo Daliji and Yueku stitch treatment twice a week for 12 weeks. All of the researchers in the study will receive professional training on prediabetes before participating. All acupuncturists will receive the same training under the clinical treatment plan before the study to standardize the procedures performed by the different acupuncturists. During the trial, in addition to the research interventions, other treatments for blood glucose control will be prohibited.

#### Lifestyle intervention

2.7.1

Patients in both groups will receive basic health management and lifestyle modification over the course of the 12-week study period. Lifestyle intervention is implemented with reference to the goal of primary prevention of type 2 diabetes in the Guidelines for the Prevention and Treatment of Type 2 Diabetes (2017 Version) in China.^[14]^

The first lecture on prediabetes will be held when the study begins, which is to include the development and prevention of diabetes. Prediabetes health education courses will be performed once a month. Course content includes:

(1)Diet: patients will be instructed to focus on low-sugar, low-salt, light and easily digestible foods, limit the total daily calories intake, reasonably control cholesterol and fat intake, and control body weight.(2)Living habits: patients will be instructed to work and rest on time. Bad habits such as smoking and drinking will be strictly controlled. Require patients to adhere to 50 minutes of moderate-intensity aerobic exercise at least 3 times per week.(3)Psychology: patient will be received psychological therapy to relieve patient's pressure, and to inform the patient that the cure or delay of prediabetes progress is likely. It should be treated with a positive and optimistic attitude, and do not be afraid or let it develop.

Researchers will personally understand the patient's lifestyle habits such as diet, rest time and exercise, and give reasonable personalized lifestyle suggestions. The researchers supervised the implementation of the prevention and treatment plan through telephone or Internet follow-up, encouraging family members to participate in intervention management methods to improve the self-management ability of prediabetes patients.

#### Acupuncture intervention

2.7.2

This acupuncture intervention complies with the Standards for Reporting Interventions in Clinical Trials of Acupuncture^[15]^ guidelines. Participants in the treatment group will be treated with Zuo Daliji stitch treatment combined with Yueku stitch treatment. Daliji acupuncture points include Zusanli (ST36), Zhigou (TE6), Taibai (SP3). And Yueku acupuncture points include Taichong (LR3) and Dacha. The location of acupuncture points is shown in Figure 2. The Dacha is a new acupoint discovered by professor [name]. It is located between the 1st and 2nd metacarpal bones of the hand and takes the middle point of the red and white meat line with a semi-clenched fist. Disposable, sterile steel, 0.14 × 25 mm or 0.14 × 40 mm acupuncture needles (Eaku disposable acupuncture needles, Maanshan Bond Medical Devices Co, Anhui, China) will be used for the acupuncture treatment. Each needle is equipped with a separate needle insertion tube.

**Figure 2 F2:**
[figure not shown]
Acupuncture point positioning.

##### Acupuncture manipulation

2.7.2.1

The patient remained supine, and the researchers routinely disinfected each acupuncture point. The specific operation is as follows.

###### Yueku acupuncture treatment

2.7.2.1.1

Dacha: Pat the needle gently under the skin at Dacha Point. Remove the needle tube and hold the needle handle and twist the needle gently towards the joint of 1st and 2nd metacarpal bones. At the same time, let the patient breathe slowly and deeply to feel the depth and smoothness of the breath. When the tip of the needle approaches the junction of the first and second metacarpal bones, the needle is raised back into the skin. Operate as described above for 3 to 5 times, and keep the needle.

Taichong (LR3): Gently pat the needle into the skin at a 30° to 45° angle at Xingjian (LR2). Take out the needle tube and hold the needle handle so that the tip of the needle points towards the direction of Taichong Point. After the tip of the needle reaches the Taichong point, the needle is brought back to the skin, and then operated 3 to 5 times as described above, and the needle is left. The patient also needs to breathe slowly and deeply during the acupuncture.

###### Daliji acupuncture treatment

2.7.2.1.2

The acupuncturists use the above needle insertion method to insert the needle vertically in Zusanli (ST36), Zhigou (TE6), Taibai (SP3), with a depth of about 1 to 2 cm, until the doctor feels that the needle is tightly sucked by the muscle to keep the needle.

**2.7.2.1.2.1 Needle insertion sequence**

The sequence of acupuncture is Taichong (LR3), Dacha, Taibai (SP3), Zhigou (TE6), Zusanli (ST36).

**2.7.2.1.2.2 Needle out sequence**

After taking out the needles in the order of Taichong (LR3), Dacha, Zhigou (TE6), and Zusanli (ST36), let the patient overlap their hands on the lower abdomen, and still breathing slowly and deeply, focusing on Dantian (Qihai (RN6) acupoint). After 5 minutes, take out the needle at Taibai (SP3).

**2.7.2.1.2.3 Treatment course**

The acupuncture session will be for 45 minutes. There will be 2 sessions per week for 12 weeks, giving 24 sessions in total.

### Outcome measures

2.8

Data collection will be performed by a trained and nonparticipating evaluator who is blinded to the patient's assignment, including at baseline, the intervention phase (4 weeks, 8 weeks, and 12 weeks) and at the end of follow-up (24 weeks).

### Primary outcomes

2.9

The Primary outcomes is the conversion rate from prediabetes to normal blood glucose. Normal blood glucose means FBG and 2-hPG (OGTT) are in the normal range (FBG < 6.1 mmol/L, 2-hPG < 7.8 mmol/L).

Conversion rate = cases converted to normal blood glucose ÷ total cases of each group ×100%

### Secondary outcomes

2.10

Secondary outcomes include the following: FPG, 2-hPG after a 75-g OGTT, glycosylated hemoglobin and blood lipid concentration.

FBG and 2h-hPG will be tested at visit 1 (3 days before study), visit 4 (week 12) and the end of follow-up period. Other secondary outcomes will be tested only at visit 1 and visit 4 (Table 1).

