## Statistical analysis

5

In this study, the conversion rate from IGT to normal blood glucose between baseline and follow-up period was the main outcome indicator. Statistical analysts will use a one-sided *t* test to compare between the 2 groups. The 2 groups will be compared using the 95% confidence interval method to determine the advantage. Data will be statistically analyzed using PASW Statistics 18.0 (IBM SPSS Inc., Armonk, NY) and SAS 9.2 software (SAS Institute Inc., Cary, NC). For secondary results, a 2-tailed *P* value *<* .5 will be considered statistically significant. For safety evaluation and analysis, first use descriptive analysis, and then use tests to compare the incidence of adverse reactions between the 2 groups. When comparing, consider the severity of adverse reactions and the degree of causation with the intervention. The categorical variables between the 2 groups were compared using Fisher exact test and chi-square test.

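### Every comparison the plan names is unadjusted, although baseline values of all glucose and lipid outcomes are collected; baseline adjustment would add precision at almost no cost

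*Protocol article*

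**What the plan says.** Secondary outcomes (2.10) sets the measurement schedule: "FBG and 2h-hPG will be tested at visit 1 (3 days before study), visit 4 (week 12) and the end of follow-up period". For HbA1c and lipids, "Other secondary outcomes will be tested only at visit 1 and visit 4". Every laboratory outcome therefore has a baseline value.

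Primary outcomes (2.9) builds the endpoint from two of these variables: "Normal blood glucose means FBG and 2-hPG (OGTT) are in the normal range (FBG < 6.1 mmol/L, 2-hPG < 7.8 mmol/L".

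Statistical analysis (5) names these comparisons:

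- directly after the sentence on the main outcome: "Statistical analysts will use a one-sided *t* test to compare between the 2 groups";
- then: "The 2 groups will be compared using the 95% confidence interval method to determine the advantage";
- for categorical data: "The categorical variables between the 2 groups were compared using Fisher exact test and chi-square test".

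For the secondary outcomes it fixes only a threshold: "For secondary results, a 2-tailed *P* value *<* .5 will be considered statistically significant". It names no test or model for them and does not say whether follow-up values or changes are compared. No covariate, ANCOVA or regression model appears anywhere in the article. The randomisation section (2.6) describes 1:1 blocks and names no stratification factor.

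**The concern.** Conversion is a cut of the same two glucose values that are measured at baseline, and the inclusion criteria (2.4) admit people at very different distances from the cuts. Someone with isolated impaired fasting glucose is at most 7.0 − 6.1 = 0.9 mmol/L above the fasting cut and already below the 2-hour cut. Someone with impaired glucose tolerance may be up to 11.1 − 7.8 = 3.3 mmol/L above the 2-hour cut. Starting distance plausibly predicts conversion, although the article gives no figure for how strongly.

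With 30 per arm, a named analysis that leaves this information out yields wider intervals than the collected data allow, and the estimate does not account for whatever baseline difference happens to arise. Precision and accuracy given the observed baseline are at stake. The validity of the randomised comparison is not.

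**Working it through.** **Inputs from the article.** Conversion 57% against 20%, α = 0.05, β = 0.2, 25 per group, 15% dropout, 30 per group (Sample size, 2.2). **Assumed, because the article gives no figure:** baseline-to-follow-up correlation r of 0.3 to 0.7, and the strength with which baseline predicts conversion.

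**1. The plan's own figure.** For two proportions, two-sided α = 0.05 and 80% power:

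- Unpooled: n = (0.57×0.43 + 0.20×0.80) × (1.960 + 0.842)² / 0.37² = 0.4051 × 7.85 / 0.1369 = 23.2, so 24 per group.
- Pooled variance under the null, no continuity correction: 26 per group.
- Dropout: 25 / 0.85 = 29.4, so 30 per group.

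The stated 25 lies between the two versions. The calculation uses no baseline covariate and is not in error on this point.

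**2. Chance baseline difference.** The standard error of a baseline mean difference, in SD units, is √(2/n).

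| Per arm | SE (SD) | P(gap > 0.25 SD) | P(gap > 0.5 SD) |
|---|---|---|---|
| 30 | 0.258 | 33% | 5% |
| 25 | 0.283 | 38% | 8% |

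These figures hold for any trial of this size.

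**3. Continuous outcomes.** Relative to comparing follow-up values only (variance 1), comparing changes has variance 2(1 − r) and ANCOVA has 1 − r². ANCOVA relative to change scores is (1 − r²) / [2(1 − r)] = (1 + r)/2. The equivalent unadjusted total is 60 / (1 − r²). The detectable difference at 80% power, two-sided 0.05, 30 per arm, is 2.80 × √(2/30) = 0.72 SD unadjusted, multiplied by √(1 − r²) for ANCOVA.

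| r (assumed) | Change score, variance | ANCOVA, variance | Equivalent total | Detectable difference (SD) | ANCOVA / change score |
|---|---|---|---|---|---|
| 0.3 | 1.40 | 0.91 | 66 | 0.69 | 0.65 |
| 0.5 | 1.00 | 0.75 | 80 | 0.63 | 0.75 |
| 0.7 | 0.60 | 0.51 | 118 | 0.52 | 0.85 |

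If changes were analysed, baseline would already be used, but less efficiently than by ANCOVA, and below r = 0.5 less efficiently than by follow-up values alone.

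**4. Conversion.** Simulation with 25 per arm, marginal rates 57% and 20%, 4000 trials per row, and a linear model with and without one standardised baseline covariate:

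| Log-odds per SD (assumed) | Variance, adjusted / unadjusted | Power, unadjusted | Power, adjusted |
|---|---|---|---|
| 0 | 1.01 | 81% | 78% |
| 0.5 | 0.98 | 82% | 81% |
| 1.0 | 0.87 | 80% | 83% |
| 1.5 | 0.79 | 81% | 89% |

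The simulation standard error of a power near 80% is √(0.8 × 0.2 / 4000) = 0.6 percentage points, so the spread in the unadjusted column is largely noise. A separate simulation with a logistic likelihood-ratio test gave 81% rising to 84% or 88% when the covariate predicted conversion with an AUC of 0.71 or 0.77. That test ran at 5.5% to 6.4% under the null, so part of its apparent gain may be inflation.

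**5. Size of model the data can carry.** Expected conversions with 25 per arm are 25 × 0.57 + 25 × 0.20 = 19.25, about 20.

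**The case against.** The strongest reply is that an unadjusted comparison in a randomised trial is valid, and that an article may leave the model for secondary outcomes to an analysis plan that is not shown. Both parts stand, and they rule out several stronger readings.

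- A reader might infer that the secondary analyses ignore baseline. The article does not show this. It names no test for those outcomes, and the t test sentence follows the sentence on the main outcome. The equivalents of 66 to 118 participants apply only if follow-up values alone would otherwise be compared.
- A reader might infer that chance imbalance biases the result or inflates the type I error. It does not: the error rate of the unadjusted test already covers chance imbalance. The 33% figure describes ordinary sampling variation at an arbitrary threshold.
- A reader might infer that adjustment would lift the power of the primary test. It would not while an unadjusted test decides, and with a weak or useless covariate the simulated adjusted power was no better or slightly lower.
- A reader might take the missing stratification factor as a fault. Unstratified blocks are acceptable, and an article may leave such detail to the full protocol.

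It is also fair to say that the narrow eligibility windows for glucose tend to lower r, so the 0.3 row should not be dismissed.

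What the reply does not remove is that the section does name methods, that all of them are unadjusted, and that the baseline of the very variables defining the endpoint is available.

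**Conclusion.** The point holds as an efficiency improvement, not as an error of validity. The named comparisons make no stated use of baseline FPG and 2-hPG, and no stated method uses baseline for the continuous secondary outcomes.

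For continuous outcomes, ANCOVA would cut the variance by 9% to 49% against a follow-up-only comparison (r from 0.3 to 0.7), or by 35% to 15% against change scores over the same range. For the conversion estimate the gain runs from none to about 21% of the variance, and the power of the primary test is unchanged under the fix below.

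All these sizes rest on assumed correlations and prognostic strengths. The conversion figures also come from a linear model with one covariate, not from the two-covariate logistic standardisation proposed below. The point ranks below two plainer problems in the same section, the t test for a proportion and the printed significance threshold for secondary results.

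**What to change.** In Statistical analysis:

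- **FPG, 2-hPG, HbA1c and lipids:** specify ANCOVA, with the follow-up value regressed on arm and the outcome's own baseline value, at each visit where the outcome is measured. Report the adjusted mean difference with its 95% confidence interval.
- **Conversion:** keep an unadjusted test of proportions (chi-square or Fisher's exact test, one of them named) as the decision rule. Add a supporting risk difference with 95% confidence interval, standardised from a logistic model with arm, baseline FPG and baseline 2-hPG.
- **Timing:** fix the models and covariates before any outcome data are seen by arm, so that covariates are not chosen after an imbalance appears.

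The cost is a few sentences in a section that needs rewording anyway and a few lines of SAS, with no new visits, measurements or participants. The one downside is that, with about 20 conversions expected, the logistic model should hold no more than these two covariates besides arm.
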